**Impact on participants' partners (OBJECTIVE 3 and 9):**

- Questionnaires results

**Neural signature of meditation practices (OBJECTIVE 5) :**

- Measure of neural activity in all brain voxels measured with resting-state fMRI as well as with fMRI during the SOVT-Rest task, in a mindfulness state versus a non-meditative state.  
Measure of neural activity in all brain voxels measured with resting-state fMRI as well as with fMRI during the SOVT-Rest task, in a compassion state versus a non-meditative state.

**Safety and acceptance (OBJECTIVE 2, 3ter):**

- Adverse events, measures of anxiety, depression, satisfaction, and well-being.

## Statistical aspects

---

The statistical analysis of the primary outcomes (objectives 1 + 1bis) will be conducted by the biostatistician team of EUCLID. Details of the statistical aspects regarding the primary objectives are listed in the corresponding Statistical Analysis Plan written by EUCLID.

The statistical analysis of secondary outcomes will be performed by respective WPs dedicated to the evaluation of the different objectives as follows:

WP1 Meditation: [name]

WP2 Lifestyle: [name]/[name]

WP3 Attention: [name]

WP4 Emotion: [name]

WP5 Cognition and Wellbeing: [name]

WP6 Biomarkers: [name]

### Analysis strategy

#### Definition of analysis populations

The statistical analyses for the main objectives (primary endpoints) are described in the corresponding document.

For the secondary objectives (secondary endpoints) two types of analyses will be performed:

Analyses will be performed in intent to treat. All randomized participant will be included in the analysis in the group to which they were initially randomized and all their data is used, regardless of protocol deviations during the trial. Any missing value (missing= failure) will be replaced by the value corresponding to failure.

In order to assess the robustness of the results, a sensitivity analysis for the missing data will be performed using the maximum bias strategy using values reflecting failure and success (minimum and maximum difference, respectively) estimated on the observed data of all groups.

In addition, "per protocol" analyses will be performed: Participants' data will be analyzed in the group according to the treatment they actually received. Per protocol population includes "participants who attended at least 20% of intervention classes, or neither meditation nor foreign language training for participants in the passive control group.

For exploratory analyses not related with the intervention (e.g. analyses on baseline data independent from intervention group), all participants will be included in the analyses.

Decisions about which of these analysis strategies should be used will depend on the specific analyses and decided by the PI and validated by the ExCom.

Only participants presenting at least one of the following conditions can be excluded from the analysis:

- participants wrongly included with an unsigned consent;
- participants wrongly included for major non respected eligibility criteria;
- participants who withdrew their informed consent.

Decisions about exclusion will be made by the Trial Scientific Committee after documentation of observations by the EUCLID platform, blinded to the strategy group and to the participants' evolution after enrolment.

Except for these exclusions, the participants who died or who were lost to follow-up, or who interrupted the intervention or who left the study will all be included in the analysis.

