- Anthropometric measurements (weight (kg), fat (%), fat mass (kg), lean mass (kg), hydration rate (kg), muscle mass (kg), bone mass (kg), impedance (Ohm), basal metabolic rate (kJ; kcal), visceral fat (level) and metabolic age (year), as well as BMI, Sarcopenic Index (SMI; kg/m^2) and Skeletal Muscle Mass (SMM; kg and %).
- Charlson and CIRS scores
- Impact on the participants' entourage (OBJECTIVE 3):
  - Scores from the questionnaires given to the participants' partners as listed in Tables 5 and 6 below.
  - Qualitative data from interviews with participants and teachers.
- Neural signature of meditative practices (OBJECTIVE 5):
  - Measurement of neural activity in each brain voxel in fMRI at rest, and during the rest-SOVT task, in a mindfulness meditation state versus a non-meditative state ;
  - Measurement of neural activity in each brain voxel in fMRI at rest, and during the rest-SOVT task, in a compassionate meditative state versus a non-meditative state.
- Measurement of the tolerance to the intervention (OBJECTIVE 2):
  - Occurrence of adverse events;
  - Anxiety measured by the State-Trait anxiety Inventory (STAI);
  - Depression as measured by the Geriatric Depression Scale (GDS);
  - Positive and negative emotions measured by the questionnaire PANAS-NOW;
  - Satisfaction and well-being measured by self-questionnaires.

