### **8.3.6. Potentiel risks of the intervention and trial, and what to do in case of an adverse event**

The expected risks in this trial are described in chapter 14.1.

In the event of an adverse event, the course of action is the usual medical management .

In order to limit the appearance of undesirable effects in the participants during the meditation training, a preliminary interview will be organized with one of the meditation teachers. If these effects appear, a follow-up will be set up with a psychotherapist. Finally, if these side effects become too severe, a termination of participation in the meditation intervention will be proposed.

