#### **11.3.1. Analysis strategy**

The main analysis will be carried out on an intention-to-treat basis, i.e. all randomized patients will be included in the analysis in the group in which they were initially randomized, and all their data will be used regardless of their changes in strategy during the research, with the "missing = failure" strategy, i.e. any missing value will be replaced in the analysis by the value corresponding to failure (minimum difference between 18 months after the intervention and inclusion), estimated on the data observed in all groups combined.

In order to assess the robustness of the results, a sensitivity analysis to missing data will be performed using the maximum bias strategy by using the values reflecting the failure and success (minimum and maximum difference respectively) estimated on the observed data for all groups combined.

A sensitivity analysis will also be performed by including only participants who attended at least 20% of the meditation sessions and exercises and who completed the examinations for the primary judgement criterion.

Some features may be strongly associated with volume and perfusion of the anterior cingulate cortex or insula. These characteristics could play a confounding role if, despite randomization, an imbalance was observed. Therefore, the comparative analysis of the primary judgemental criteria could be adjusted for potential confounders such as age, education, and gender. These adjustments may require the use of appropriate models, the relevance of which will be discussed according to the distribution and type of variables.

The description will always be done globally and by treatment group.

Tests for the primary criteria will be performed at the risk of error of the first kind  $\alpha = 1.25\%$ .

Tests for secondary criteria will be performed at the overall risk of error of the first kind  $\alpha = 5\%$ .

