### Conventions for the calculation of the change (delta) of measurement between 2 visits

The difference between two measurements, one taken at D00 and a second taken at a visit posterior to D00 (follow-up visit DXX) will be calculated using the following formula:

- Delta = (measurement at DXX – measurement at D00)

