#### Secondary objectives

##### *Objective 2 (WP 1 to 6)*

For the main secondary outcome, the difference between the inclusion and 18 months of i) the global metacognitive composite score, and ii) the attentional, constructive and deconstructive subscores, will be compared between the meditation intervention and language learning intervention groups.

These scores will be computed as described in (Schlosser et al., Submitted). Briefly, the metacognitive composite score drew from the following self-report measures employed in the Age-Well randomised controlled trial (See Poisnel et al. for details and corresponding references): the Compassionate Love Scale (CLS; stranger-humanity version), the Drexel Defusion Scale (DDS), the Five Facet Mindfulness Questionnaire (FFMQ), the Interpersonal Reactivity Index (IRI), the Multidimensional Assessment of Interoceptive Awareness Version 2 (MAIA-2), and the Prosocialness Scale. Amongst those, seven subscales were judged to primarily capture attentional aspects: noticing (MAIA subscale), attention regulation (MAIA), emotional awareness (MAIA), self-regulation (MAIA), body listening (MAIA), observing (FFMQ), and acting with awareness (FFMQ). Four (sub)scales were judged to primarily capture constructive aspects: the CLS, empathic concern (IRI subscale), perspective taking (IRI), and the Prosocialness Scale. Another four scales were judged to primarily capture deconstructive aspects: the DDS, non-judging (FFMQ), non-reactivity (FFMQ), distress (IRI).

To compute each composite score, scale scores will be first standardised using their baseline mean and standard deviation, and the sum of the standardised scale scores will then be divided by the number of scales included in the respective composite. Scales will be reverse-scored if higher total scores reflect worse functioning. Ergo, higher composite scores will indicate higher capacities in the psychological processes characterising the three meditation families. Participants with missing scale scores will not be included in the composite score to which this scale is assigned.

The evolution of the same scores in the passive control group will be provided for the sake of description. Moreover, the difference between the inclusion and 18 months of all additional composite scores and individual behavioural cognitive, psychoaffectives, life, blood, sleep and imaging measures will be compared between

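### For secondary outcomes where lower is better and scores are not reversed, such as anxiety and depression, the missing = failure rule read literally imputes the best change seen in the trial

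*Combined protocol and SAP*

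**What the plan says.** In the secondary SAP, Definition of analysis populations, the intention-to-treat rule for secondary endpoints is: "Any missing value (missing= failure) will be replaced by the value corresponding to failure". That sentence does not say what failure is. The next one, on the maximum bias sensitivity analysis, does: "using values reflecting failure and success (minimum and maximum difference, respectively) estimated on the observed data of all groups". Protocol section 11.3.1 ties the same definition to the missing = failure rule of its main analysis: "minimum difference between 18 months after the intervention and inclusion), estimated on the data observed in all groups combined". Primary SAP section 3.6.1 also defines failure as the minimum change.

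The sign of a change score is fixed in the secondary SAP's calculation conventions as follow-up minus baseline: "Delta = (measurement at DXX – measurement at D00".

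The secondary SAP's safety and acceptance outcomes are "Adverse events, measures of anxiety, depression, satisfaction, and well-being". Protocol section 5.2 names STAI and GDS as the anxiety and depression instruments for tolerance.

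Reverse scoring appears in one place only, under Objective 2, for the metacognitive composite and its three subscores. The same paragraph gives those scores a different missing-data rule: "Participants with missing scale scores will not be included in the composite score to which this scale is assigned".

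**The concern.** The minimum of follow-up minus baseline is the worst change only where higher is better. That suits the primary outcomes, regional volume and perfusion, where the hypothesised benefit is an increase. On a scale where higher is worse, the minimum is the largest improvement anyone had. Each participant with a missing value would then be credited with the trial's best result on that scale.

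The affected scores include the two that are meant to detect psychological harm from the interventions. Protocol section 8.3.6 foresees that harm, stating that "if these side effects become too severe, a termination of participation in the meditation intervention will be proposed". If values are missing more often on meditation, the rule pulls the comparison toward benefit on these scales. Measures with no natural adverse direction, such as connectivity or magnetic susceptibility, have no meaningful failure value at all.

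**Working it through.** **Inputs from the documents.** Planned enrolment is 150, so 50 per arm (secondary SAP, Sample size). Tests of the other secondary endpoints are two-sided at 5% (Type I error rate). The one sample-size figure, 42 per arm for an effect of 0.75 at 80% power and two-sided 1.25%, reproduces: the normal approximation gives 40, and the noncentral t gives 79.7% power at 41 and 80.9% at 42. It does not depend on the failure definition.

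**Assumptions.** Change SD is 1. STAI and GDS are scored higher = worse, which the documents do not state. Missingness is random within arm. Arms are compared by t test. Protocol section 11.2 calls the dropout risk very low and gives no number, so a range is shown.

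**Formula.** Let δ be the true meditation-minus-control difference (positive = harm), pM and pC the proportions missing, and m the pooled observed minimum. The expected estimate is

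(1 − pM)·δ + (pM − pC)·m

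By simulation with three arms of 50, m is about −2.6 SD when δ = 0 and about −2.5 SD when δ = 0.5.

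**No true effect**
- 10% vs 2%: 0.08 × (−2.6) = −0.21 SD, a false benefit. It is significant in favour of meditation in 14% of runs with random dropout counts and in 11% with counts fixed at 5 and 1. The nominal rate in one direction is 2.5%.
- 10% vs 4%: −0.16 SD, significant in 6%.
- 20% vs 4%: −0.42 SD, significant in 34%.
- 4% vs 20%: +0.42 SD, a false harm, significant in 34%.
- 2 vs 1 participants missing: −0.05 SD, significant in 3.0%.
- 10% vs 10%: 0.00 SD, no directional bias.

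**True harm of +0.50 SD on meditation** (detected in about 70% of runs with complete data)

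| Missing, meditation / control | Literal rule (minimum): estimate, harm detected | Corrected sign (maximum): estimate, harm detected |
|---|---|---|
| 10% / 10% | +0.45, 39% | +0.45, 41% |
| 10% / 4% | +0.30, 17% | +0.62, 81% |
| 20% / 4% | −0.01, 0.4% | +0.85, 97% |
| 4% / 20% | +0.87, 97% | +0.02, 0.6% |

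The formula agrees. For 20% / 4%, 0.8 × 0.50 + 0.16 × (−2.54) = −0.01.

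The last column shows that the right sign alone is not enough. Filling gaps with one extreme value turns a true +0.50 SD into +0.85 or +0.02 SD, depending on which arm loses more.

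**Maximum bias analysis.** It is run both ways, so exchanging the failure and success labels gives the same pair of results: −0.52 and +0.52 SD at 10% / 10% with no true effect.

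**The case against.** The best case for the plan is that the intention-to-treat sentence says only that failure is imputed, and nobody would call the best improvement a failure. The minimum-difference wording sits in the sensitivity sentence, and the protocol's version was written with volume and perfusion in view. This shows the literal reading may not be what the authors meant. It does not supply another rule: every definition in the documents is the minimum, and none is tied to an endpoint's direction.

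Four stronger readings are tempting, and the documents do not support them.
- A reader might infer that every secondary endpoint, or every lower-is-better scale, is affected. The metacognitive composite and its subscores are reverse-scored, and adverse-event occurrence is not a change score.
- A reader might infer that the rule will hide harm. That requires more missing data on meditation. Protocol section 6.15.1 keeps people who stop the intervention in follow-up, the SAP allows those who withdraw consent to be excluded, and adverse events are recorded separately. Informative loss is plausible but not established.
- A reader might infer that the maximum bias analysis is also wrong. It is symmetric in the two labels.
- A reader might infer that excluding participants with a missing scale guts the main secondary outcome. Treating its 15 (sub)scales at two visits as independently missing at 1% or 2% gives 1 − 0.99³⁰ = 26% or 1 − 0.98³⁰ = 45% lost. But the scales come from six questionnaires, and 1 − 0.99¹² = 11% or 1 − 0.98¹² = 22% is nearer the mark under the same assumed rates. The Objective 2 rule can also be read as a specific exception to the general one. The SAP only needs to say so.

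The secondary SAP also lets the principal investigator choose the strategy for each analysis, with ExCom validation. A better method may therefore be used, but the stated rule stays wrong and the choice is not fixed in advance.

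**Conclusion.** The rule is wrong as written for secondary outcomes where lower is better and scores are not reversed, and it has no meaning for measures without a direction. This is more than missing detail: applied literally, it gives each missing value an improvement of about 2.6 SD.

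The resulting bias is about 0.026 SD per percentage point of between-arm difference in missingness. It favours whichever arm loses more and largely disappears when losses are equal. With one or two participants missing it is negligible; at 20% versus 4% it cancels a true 0.50 SD harm. These sizes rest on the assumed dropout rates, higher-is-worse scoring of the affected scales, and a pairwise t test with 50 per arm. Most of the magnitude comes from single extreme-value imputation; the undirected definition decides which way it points.

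**What to change.** Before unblinding, amend the secondary SAP as follows.

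1. List the adverse direction of each secondary endpoint and define failure as the worst observed change in that direction. Do not apply the rule to measures with no direction, such as connectivity or susceptibility.
2. For repeatedly measured outcomes such as STAI and GDS (V1, V2 and V3 in protocol Table 5), make the mixed model already named under Objective 2, on all available data, the main analysis.
3. Keep the correctly signed missing = failure analysis and the maximum bias analysis as sensitivity analyses.
4. Add one sentence saying whether the general imputation rule or the Objective 2 exclusion rule governs the metacognitive composite.

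The cost is SAP wording and a direction flag per outcome. No new data are needed.

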### 2.1 Analysis strategy

#### 2.1.1 Definition of analysis populations

Only participants presenting at least one of the following conditions can be excluded from the analysis:

- participants who never followed the study strategy (if they had no knowledge of the group they were randomized in);
- participants wrongly included with an unsigned consent;
- participants wrongly included for major non respected eligibility criteria;
- participants who withdrew their informed consent.

Decisions about exclusion will be made by the Trial Scientific Committee after documentation of observations by the EUCLID platform, blinded to the strategy group and to the participants' evolution after enrolment.

Except for these exclusions, the participants who died or who were lost to follow-up, or who interrupted the intervention or who left the study will all be included in the analysis.

Intent to treat analysis: All randomized participant will be included in the analysis in the group to which they were initially randomized and all their data is used, regardless of protocol deviations during the trial.

Per protocol analysis: randomized participants who attended at least 20% of their allocated interventions classes, or neither meditation nor foreign language classes if in the passive control group, and with primary endpoints available.

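### The secondary SAP's per-protocol analysis groups by treatment received, unlike the primary SAP, and intention to treat is not fixed as the main result for the randomised secondary comparisons

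*Combined protocol and SAP*

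**What the plan says.** The secondary SAP opens its section on analysis populations with "For the secondary objectives (secondary endpoints) two types of analyses will be performed". Intention to treat comes first: "All randomized participant will be included in the analysis in the group to which they were initially randomized". A per-protocol analysis is then added, with two rules in consecutive sentences. The grouping rule is "Participants' data will be analyzed in the group according to the treatment they actually received". The membership rule admits "participants who attended at least 20% of intervention classes, or neither meditation nor foreign language training for participants in the passive control group". After a sentence on baseline-only analyses, the section states that the choice among these strategies "will depend on the specific analyses and decided by the PI and validated by the ExCom".

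The primary SAP, §2.1.1, uses the same label for "randomized participants who attended at least 20% of their allocated interventions classes, or neither meditation nor foreign language classes if in the passive control group", with primary endpoints available. It has no sentence on grouping by treatment received. The protocol (11.3.1) plans only a sensitivity analysis restricted by attendance, and it moves nobody between groups.

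Under Type I error rate, the secondary SAP controls error for one main secondary outcome (meditation against English, then three subscores with Bonferroni). Every other secondary test is run at 5%.

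**The concern.** A per-protocol analysis normally restricts the randomised arms. Grouping by treatment received is a different analysis, because membership of an arm then depends on what participants did after randomisation, and the comparison loses the protection of the random allocation. Here both ideas share one label, and that label means something else in the companion SAP. Two analysts could build different data sets from the same text.

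The second sentence at issue matters more widely. If the strategy can be settled analysis by analysis, across cognitive, psychoaffective, lifestyle, sleep, blood and imaging outcomes, a reader of the results cannot tell whether the reported population was fixed in advance. Running most of these tests at 5% each means that multiplicity control does not limit the consequences of that choice.

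**Working it through.** **Step 1: apply each definition to the same participants.** The plan gives no figure for this analysis, so the check begins with the wording.

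| Participant | Primary SAP §2.1.1 | Secondary SAP |
|---|---|---|
| Randomised to meditation, attended 20% or more of meditation classes | In, meditation | In, meditation |
| Randomised to meditation, attended 20% or more of English classes instead | Out (not the allocated classes) | Meets the filter as worded; analysed as English |
| Randomised to meditation, attended nothing | Out | Plain reading: out. Other reading: placed by treatment received |
| Randomised to passive control, attended neither | In, passive | In, passive |

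The two documents clearly part company in the second row. Crossover is foreseen: protocol 6.8 asks participants not to take up the other arms' activity, and primary SAP §3.2 lists receipt of the wrong intervention as a deviation.

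**Step 2: the non-attender row.** Someone randomised to an active arm who attended nothing fails the 20% route. The other route is worded for passive control participants, so the plain reading excludes this person. Two features leave doubt. The grouping sentence defines groups by what was received. The list of permitted exclusions is also introduced as the only one: it has three conditions, omits the never-followed condition that appears in the primary SAP, and keeps in everyone who interrupted the intervention. That list may be meant for the intention-to-treat set, but the section does not say so.

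**Step 3: who decides.** The promise of two types of analysis and the later sentence about which to use do not fit together. Decisions to exclude participants must be made blind to group, but nothing similar is required for the choice of strategy. Neither Type I error rate nor Objective 2 names a population for the main secondary outcome.

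**Step 4: size, for illustration only.** The documents give no non-attendance rate. Inputs: n = 50 per arm (42 + 8, from the sample size section). Assumed: a fraction q of each arm are non-attenders, their mean change is g = 0.5 SD worse than that of attenders, there is no true effect, and all outcomes are observed. Set each full arm's mean to 0. Attenders then average +qg and non-attenders qg − g.

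- Intention to treat: difference 0.
- Non-attenders excluded, arms as randomised: meditation minus passive = qg. For q = 0.10 this is 0.10 × 0.5 = 0.05 SD; for q = 0.20 it is 0.10 SD.
- Non-attenders of both active arms placed with passive control. For q = 0.10, ten people with mean 0.05 − 0.5 = −0.45 join 50 with mean 0, so the enlarged control mean is −4.5/60 = −0.075 and the difference is 0.05 + 0.075 = 0.125 SD. For q = 0.20, twenty people with mean −0.40 join, the control mean is −8/70 = −0.114, and the difference is 0.10 + 0.114 = 0.21 SD. For q = 0.02 (one person per arm), the difference is 0.01 + 0.98/52 = 0.03 SD.
- Meditation minus English: both arms lose the same fraction, so the difference is 0 under either reading. Only crossover or unequal attendance would affect it.

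**The case against.** The strongest reply is that little changes in practice. Intention to treat is stated first and per protocol is an addition. The sentence on choosing a strategy follows the one on baseline-only analyses, so it can be read as matching strategy to type of analysis. The PI does not decide alone, since the ExCom must validate. The secondary SAP needs steering committee approval before any analysis (Purpose), the sponsor keeps a record of all tests (protocol 11.3.7), and those analysing data do not know allocation (protocol 3.2). Dropout after allocation is expected to be very low (protocol 11.2), and willingness is confirmed by telephone before randomisation (6.7).

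Much of this stands as a limit on size. It does not settle the wording. Approving a SAP that contains an open choice leaves the choice open. A log of tests does not say which one is the main result. The ExCom is the consortium's own committee, which also decides on analyses and publications (protocol 12.1).

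A reader might also infer that participants who never attend are turned into passive controls, with the larger differences in Step 4. The documents do not say so: the route for those who attended neither training is limited to passive control participants. On the plain reading, non-attenders are treated as the primary SAP treats them, and adopting its rule would change nothing for them. Nor do the documents support a reading in which the PI chooses alone or only one analysis is run.

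**Conclusion.** The point holds as a defect of definition and pre-specification in the secondary SAP. Three things follow from the text without assumptions: the grouping rule is as-treated under a per-protocol label; the filter omits the link to allocated classes, so crossovers leave their randomised arm, contrary to the primary SAP; and intention to treat is not fixed as the main result, because the section both promises two analyses and allows a case-by-case choice.

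No size follows from the documents, which give neither crossover nor non-attendance rates. The 0.05 to 0.10 SD under exclusion rests on assumed rates of 10% to 20% and an assumed 0.5 SD deficit, and the recommended per-protocol rule shares it. That is why intention to treat should lead. The 0.125 to 0.21 SD needs the less natural reading as well. Both sets of figures concern comparisons with the passive arm, not the main secondary comparison of meditation with English. The direction depends on non-attenders doing worse. The primary analysis is unaffected. The change should be made because it is nearly free and removes a rule that breaks randomisation.

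**What to change.** In the secondary SAP, Definition of analysis populations:

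1. Delete the sentence that groups by treatment received. Use the primary SAP definition: at least 20% of the participant's allocated classes (or neither type of class for passive controls), analysed in the randomised arm.
2. Replace the PI/ExCom sentence with: *For the randomised between-arm comparisons in Objectives 2, 2ter, 3 and 3bis, ITT by randomised arm is the main result and per-protocol results are supportive and shown beside it; for the within-group analysis in Objective 2bis, groups are defined by randomised arm.* Objective 2bis is separated because the SAP assesses it within the two intervention groups.
3. Keep the all-participants rule for baseline-only analyses.

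If an as-treated analysis is wanted, give it its own label. The cost is two sentences of text, less discretion for the PI, and two results to tabulate for each comparison. No new data are needed.
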